### Secondary analysis

In order to validate data, a linear regression analysis will be computed with the DASH score as the dependent variable and treatment modality as the independent variable. Additional regression analysis will be carried out between the early crossover group and the primary treatments. A multivariate regression analysis will be conducted to adjust for potential confounders. Variables adjusted for are: age, sex, smoking, alcohol, UCLA activity, and ASA grade. Furthermore, we will analyze the longitudinal observations by applying a linear mixed-effects regression model, including modality and time as well as a modality-time interaction as fixed effects and a random intercept for each patient. Data will be summarized as coefficients with 95% CIs and variance will be summarized as *r*-squares, adjusted *r*-squares, predicted *r*-squares, and standard errors. Coefficients will be considered statistically significant if *p* values < 0.05.

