**Discussion:**

The SHAFT trial is a pragmatic multicenter RCT, that will compare the effectiveness of the main strategies in humeral shaft fracture treatment. This will include a variety of fracture morphologies, while taking the dilemmas within the population into account by splitting the population by age and providing the orthopedic society with an interval for early crossover surgery.

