### Interventions

Treatment will be performed within 14 days after injury. Eligible patients will be randomly allocated to one of two treatment options.Surgical treatmentNon-surgical treatment with the option of early crossover surgery at 6–12 weeks [17] for SHAFT-Y and at 12–26 weeks for SHAFT-E

We anticipate that surgical treatment will include plate osteosynthesis (minimal invasive plate osteosynthesis or open reduction internal fixation), intramedullary nailing (antegrade and retrograde), and external fixation. Plate and nail types, screw configurations, and surgical approaches will be decided by the surgeons. The procedure will be conducted or supervised by a senior consultant.

Non-surgical treatment will include sugar tong splint, plaster splints, hanging casts, or functional bracing such as the Sarmiento brace and will be worn until a surgeon removes it.

All patients will be advised to follow this rehabilitation protocol (Table 1).

**Table 1 Tab1:** Rehabilitation protocol

Phases (approx. timepoints)	Treatment (mobilization)	Explanation

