### Primary outcome measure

The primary outcome is the DASH score at 52 weeks [3]. The DASH will also be assessed at pre-injury, 6, 12 and 26 weeks, and 2 and 5 years. The DASH score is a 30-item self-reporting patient-reported outcome measure specific for physical function and symptoms of the upper limb. Scores range from 0 (no disability) to 100 (most severe disability). The DASH score is validated for the target population [39] and has undergone cross-cultural adaptation in Danish, Swedish and Norwegian [40].

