Recruitment of 287 humeral shaft fractures presents a challenge in a randomized setting as the annual incidence rate is 14.5 per 100.000 [54]. To overcome this, we will be recruiting from multiple sites across 3 Scandinavian countries with comparable healthcare systems and with cultural and demographic similarities. Despite these overall similarities, surgical management can differ from site to site. To prevent against bias in the surgical group, the randomization will be stratified by the study site. One drawback of this type of stratification can be the risk of open blocks in multiple sites, which can give rise to allocation bias. To limit this the randomization will be conducted in small permuted blocks.

One RCT demonstrated a statistically significant difference in a subgroup analysis between the late surgical crossover and primary surgical treatment after 12 months, favoring early surgery, with respect to possible confounding [13]. The research group has furthermore in a recent study showed the same difference between a late surgical crossover and primary successful treatment after 2 years [15]. To avoid prolonged failed treatment courses, and to minimize overall nonunion rates, the trial has implemented an option of early crossover of non-surgical treatment, if certain criteria for delayed union are met. The criteria for early crossover surgery are identical for each age group but differ regarding the time of crossover. The term “early crossover” and “delayed union” were discussed intensively by the study group. “When has the treatment failed?” Crossover to surgical treatment after non-surgical treatment is not uncommonly performed within 12 weeks for the young and is described due to lack of healing and early non-surgical failure [58, 59]. One can argue that a portion of these patients will unite without intervention [60], but multiple studies have currently shown an association between gross mobility from the fracture site to nonunion in a young population after 6 weeks [17, 50, 60]. For the elderly, our clinical experience is that healing first can be anticipated after 12 weeks. We therefore defined delayed union in SHAFT-Y between 6 and 12 weeks and SHAFT-E between 12 and 26 weeks. Furthermore, endpoints were established to create a clear timepoint of when a treatment has failed, which we believe the orthopedic society needs, since there is no consensus in nonunion for humeral shaft fractures [9, 12, 14, 61].

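### The significance test of early crossovers against the primary treatments compares a group selected after randomisation; it should be descriptive, and the trial should not be said to provide the crossover window

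*Protocol article*

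**What the plan says.** The Secondary analysis section of the protocol article plans the following: "Additional regression analysis will be carried out between the early crossover group and the primary treatments". The next sentences add a multivariable model: "Variables adjusted for are: age, sex, smoking, alcohol, UCLA activity, and ASA grade". The same paragraph ends with a significance threshold of p < 0.05 for coefficients, so the crossover regression is planned as inference.

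The section on criteria for early crossover opens the option to non-surgical patients on any one of three grounds: pain the patient cannot accept, severe pain with a clearly unstable fracture, or serious trouble with the brace. The reason is recorded for each patient.

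On timing, the Interventions section says: "Treatment will be performed within 14 days after injury". It offers "early crossover surgery at 6–12 weeks [17] for SHAFT-Y and at 12–26 weeks for SHAFT-E". For the outcome: "The primary outcome is the DASH score at 52 weeks".

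The Abstract presents the trial as "providing the orthopedic society with an interval for early crossover surgery", and the last paragraph of the main Discussion says nearly the same. Elsewhere the Discussion is more careful. It describes an earlier trial's subgroup comparison of late crossover with primary surgery as "favoring early surgery, with respect to possible confounding", and of patients operated on within 12 weeks it says: "One can argue that a portion of these patients will unite without intervention". The Secondary analysis section attaches no such caution to the trial's own comparison.

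**The concern.** The crossover group is defined by what happens after randomisation. The surgical arm is not selected on those events, and non-surgical patients who stay in the brace are those left once many of the patients doing badly have gone. A regression coefficient between these groups mixes any effect of delayed surgery with the difference in prognosis that led to crossover.

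None of the six covariates describes healing, stability, pain in the brace, brace tolerance or time since surgery. In the surgical arm the reasons for crossover cannot be observed at all, because no one there was tried in a brace. Adding covariates would therefore not fully repair the contrast.

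At stake is a significant coefficient being read as evidence that delay harms, or that crossover does worse than continued bracing, when selection alone could produce it. The phrase about providing an interval invites a further step, in which the trial is taken to have shown that the window is right.

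**Working it through.** The protocol states no expected size, number of patients or power for this regression, so there is no figure of the plan's to reproduce. The checks below show direction and plausible size.

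**1. Selection, simple model.** Inputs: a 25% share of healing failures, borrowed from the Abstract's statement that about a quarter of non-surgical patients get a nonunion (the protocol gives no crossover share); DASH targets of 7 (SHAFT-Y) and 10 (SHAFT-E) from the Sample size section; and an assumed x, the DASH points by which fractures that fail in a brace do worse than those that heal, even if operated on at once. Suppose delay has no effect, and let H be the mean of the fractures that heal.

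- Surgical arm mean: 0.25(H + x) + 0.75H = H + 0.25x.
- Crossovers, all healing failures: H + x.
- Spurious difference from the surgical arm: x − 0.25x = 0.75x.
- Spurious difference from brace patients who all healed: x.

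For x = 5 to 10 (assumed), 0.75x = 3.75 to 7.5 points.

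**2. Mixed reasons for crossover.** If a share f of crossovers are healing failures and the rest cross over for other reasons with prognosis H, the difference from the surgical arm is (f − 0.25)x. With f = 0.60 (assumed) it is 0.35x, or 1.75 to 3.5 points for the same x. The bias shrinks as f falls towards 0.25.

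**3. Selection on a continuous prognosis.** Suppose no treatment affects anyone, and crossovers are the worst quarter on a latent prognosis with correlation r to DASH. The mean of the upper quarter of a standard normal variable is 0.3178 / 0.25 = 1.271, so the spurious difference from the surgical arm is r × SD × 1.271. With the protocol's SDs and r = 0.2 to 0.5 (assumed):

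- SHAFT-Y: 0.2 × 14.91 × 1.271 = 3.8; 0.5 × 14.91 × 1.271 = 9.5.
- SHAFT-E: 0.2 × 18.59 × 1.271 = 4.7; 0.5 × 18.59 × 1.271 = 11.8.

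Like step 1, this takes the crossovers to be purely the worst prognoses.

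**4. Weeks since surgery, if the contrast is read at week 52 counted from injury.**

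| Group | Surgery at week | Weeks since surgery |
|---|---|---|
| Primary surgery | 0–2 | 50–52 |
| SHAFT-Y crossover | 6–12 | 52 − 12 = 40 to 52 − 6 = 46 |
| SHAFT-E crossover | 12–26 | 52 − 26 = 26 to 52 − 12 = 40 |

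The gap to primary surgery is 4 (50 − 46) to 12 (52 − 40) weeks in SHAFT-Y and 10 (50 − 40) to 26 (52 − 26) weeks in SHAFT-E. If week 52 runs from treatment, primary surgery is at 52 weeks and the inequality remains.

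**5. The window.** Each age group has one window, the same for all its non-surgical patients, and timing within it is not randomised. The two windows differ only together with age. No planned comparison has a different window, or none, within an age group. The randomised comparison tests the non-surgical strategy with its window as a fixed component.

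**The case against.** The strongest reply is that this is one sentence among the secondary analyses, that the objective and hypothesis claim only the comparison of the two randomised strategies, and that the authors show awareness of confounding in their Discussion. All of that is true, and it limits the point to a secondary result and its wording. The sentence still fixes a comparison and the paragraph fixes a threshold, so this is not a detail left open for an analysis plan.

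Some stronger readings are not supported:

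- A reader might infer that this regression is the basis for the crossover interval. The protocol never says so. The Discussion sets the windows beforehand, from the literature for the young and from clinical experience for the elderly, and providing an interval can be read as supplying a defined window as a design feature.
- A reader might infer a bias of 3.75 to 7.5 points. That depends on an assumed x, on a nonunion figure standing in for the crossover share, and on every crossover being a healing failure, although brace intolerance also qualifies.
- A reader might take the comparator to be brace patients who did not cross over, and the time point to be 52 weeks. The section defines neither; the primary treatments could mean the arms as randomised. The contrast is confounded under either reading.
- A reader might count the shorter recovery as bias. If the question is what delay costs the patient one year after injury, later recovery belongs to the answer.
- A reader might think the 2-year DASH solves the problem. It narrows the difference in relative recovery time and leaves selection untouched.

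**Conclusion.** The concern holds in a limited form. The crossover regression is an inferential comparison of a group selected after randomisation, and its planned covariates do not remove the selection. The likely direction is that crossovers look worse than either primary treatment. This assumes that patients who meet the crossover criteria have, on average, the poorer prognosis, as criteria based on pain and instability suggest. The size is unknown; under the assumptions shown it ranges from a small part of the DASH targets of 7 and 10 to about their full size. Unequal time since surgery needs to be visible to the reader but is not necessarily an error. The trial can judge the strategy that contains the window. It cannot show that this window is better than another or than none. The primary intention-to-treat analysis does not depend on any of this.

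**What to change.** In the Secondary analysis section, state that the comparison of early crossovers with the primary treatments is non-randomised and descriptive. Report estimates with 95% confidence intervals, together with the reason for crossover and weeks since surgery, and apply no significance test. State that no causal conclusion will be drawn about delay, or about crossover versus continued bracing. The 2-year DASH, already collected as an explorative outcome, may be shown beside it as a supplement that does not cure selection.

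In the Abstract's discussion and the closing paragraph of the main Discussion, say that the trial evaluates a non-surgical strategy containing a pre-defined crossover window, and do not suggest that it establishes the window.

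The cost is a change of wording and one re-labelled secondary analysis on data already planned. The crossover result will support a weaker claim. No clinical rule changes.

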### Secondary outcome measures

Secondary outcomes consist of the DASH score, a self-reported measure of health-related quality of life (EQ-5D-5L), complication rates, visual analog scale (VAS) for pain from the arm, a functional outcome score (Constant-Murley), and anchor questions including clinical anchors, retrospective global transition questions and a binary repeat treatment question. Secondary outcome measures will be assessed at baseline, 6 weeks, 12 weeks, 26 weeks, and 52 weeks (Fig. 3):DASH score at earlier timepoints than 52 weeks (MIC [39], 7 and 10 respectively to age 18–64 and 65+)General health status questionnaire measured by EQ-5D-5L [41] (MIC [42], 0.074)Complications after treatment will be recorded and include local complications, early general complication, and mortality:Local complications: Infection (needing antibiotic treatment with or without debridement), nerve or vascular injury, surgical revision (due to implant malpositioning, hardware failure, aseptic loosening, or peri-implant fracture), and tolerance problems with a brace (discomfort resulting in non-compliance of wearing the braceEarly general complications needing hospitalization within 12 weeks from primary and secondary treatment [43, 44]:Major adverse cardiac events (MACE) including myocardial infarction, heart failure, cardiomyopathy and cardiac arrythmias.Other major adverse events include all-cause hospitalization other than the defined MACE.MortalityPain is assessed by using VAS. Patients are asked to assess their overall pain from the arm from 0 to 100 in a day (MIC [45], 16.55mm)Constant-Murley score [46] (MIC [39], 6.1). The subscales of strength and range of motion (ROM) will be depicted. ROM (flexion-extension) of the elbow will be recordedClinical anchor (CA) questions were presented with 5 response options (RO) and analyzed as a 5-point Likert scale:

Q: In general, would you say your health is?RO: Excellent, Very good, Good, Fair, Poor
*Q: How would you describe the results of the (operation/non-surgical treatment)?*
RO: Excellent, Very good, Good, Fair, Poor
*Q: How would you describe the function of your upper arm?*
RO: Excellent, Very good, Good, Fair, Poor
*Q: How would you describe the pain from your upper arm?*
RO: None, Mild, Moderate, Severe, ExtremeRetrospective global transition questions (RGTQ) presented with 5 response options and analyzed as a 5-point Likert scale:

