### Sample size

The two groups (SHAFT-Y and SHAFT-E) require individual sample size calculations. Two standard deviations (SDs) were obtained from the data of the FISH trial [13] and were separated in age groups of 18–64 years and 65 years and above. By the distribution-based approach, one half a SD corresponds to the minimal important change (MIC) [49]. The calculations are powered to detect a MIC of 7 points in the young and 10 points in the elderly group in DASH, respectively. Two independent means sample size calculations were performed. For SHAFT-Y the following data were included: mean difference = 7.0, SD= 14.91, *α*= 0.05, and power= 0.8. For SHAFT-E the following data were included: mean difference= 10.0, SD= 18.59, α= 0.05 and power= 0.8. Based on the preceding assumptions and including an attrition of 15%, the total sample size is estimated to 163 patients for SHAFT-Y and 124 patients for SHAFT-E.

The FISH trial [13] experienced 5% attrition, since more sites are involved in SHAFT the attrition is set to 15%.

The steering committee can decide to pool data from both RCTs (SHAFT-Y, SHAFT-E) if recruitment is prolonged.

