### Primary analysis

Descriptive statistics will be used to report demographic data. Demographic data and outcome measures will be tested visually and statistically (i.e., Shapiro Wilks test). Numeric variables will be summarized by means, standard deviations, and 95% confidence intervals (95% CI). Median and interquartile ranges will be used when normal distribution is not met. Categorical variables will be summarized by frequency and proportion. For group comparison with numerical data, a student’s t-test will be used if data is normally distributed, otherwise, a non-parametric test will be used. For categorical data, a chi-square test will be used for group comparison. An intention-to-treat (ITT) analysis of the primary outcome will be conducted by univariable linear regression, including all patients that do not meet the withdrawal criteria, and will be conducted to minimize bias within results. A sensitivity analysis will test the effects of non-adherence to protocol by conducting a per-protocol analysis and includes only patients who comply with the protocol. For missing data points in an outcome measure, a multiple imputation analysis using predictive covariates (age, sex, smoking, alcohol, UCLA activity, ASA grade) [50–52] will be conducted to deal with nonresponse bias. For comparison, we will carry out a sensitivity analysis excluding all the missing values.

Data will be considered statistically significant if *p* values < 0.0471.

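### The secondary longitudinal DASH model has only a random intercept, so its visit-specific and interaction standard errors depend on equal variance and equal correlation across all visits

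*Protocol article*

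**What the plan says.** The Protocol article, Secondary analysis, describes the model in one sentence. It is a linear mixed model in which treatment and time enter as main effects, followed by "as well as a modality-time interaction as fixed effects and a random intercept for each patient". It mentions no random slope, visit-specific variance, residual correlation or robust standard error. It does not say whether time is a category or a continuous variable, or which visits enter. The same section reports coefficients with 95% confidence intervals and judges them at 0.05.

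Under Primary outcome measure, the visits are listed: "The DASH will also be assessed at pre-injury, 6, 12 and 26 weeks, and 2 and 5 years". Secondary outcome measures names "DASH score at earlier timepoints than 52 weeks" as a secondary outcome.

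The primary comparison is a different model: "An intention-to-treat (ITT) analysis of the primary outcome will be conducted by univariable linear regression" (Primary analysis).

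On spread, Sample size gives one SD per age group: for SHAFT-Y "mean difference = 7.0, SD= 14.91", and for SHAFT-E an SD of 18.59. Neither is tied to a visit, and no correlation between visits is given.

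**The concern.** A patient-level random intercept with independent, equal-variance residuals implies compound symmetry: the same variance at each visit and the same correlation between neighbouring and distant visits. DASH is bounded at 0 and 100, and the visits cover very different states: before injury, in a brace or soon after surgery, then recovery, crossover or nonunion. There is little reason to expect one variance and one correlation to fit all of these.

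If variances differ, the model spreads the average variance over every visit, so each visit's treatment contrast gets the same standard error whether or not it is right for that visit. If correlations differ, the treatment-by-time interaction, which the model names as a term, gets a wrong standard error even when the variances are equal. At stake is the reliability of secondary intervals and p values from the only longitudinal model the article names.

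**Working it through.** **Plan's own figures.** The article gives no figure for this model. Its only SDs are those in the sample size. Those reproduce: n per arm = 2 × (1.96 + 0.8416)² × (SD/difference)², which is 71.2 for 14.91 and 7, and 54.3 for 18.59 and 10. Then 71 × 2 × 1.15 = 163.3 and 54 × 2 × 1.15 = 124.2, against the stated 163 and 124. They say nothing about how the SD changes by visit, so the SD patterns below are assumptions.

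**Part 1: unequal variances.** Assume complete balanced data, categorical time, and outcome visits at weeks 6, 12, 26 and 52.
- Model SE of the treatment contrast at any visit = sqrt(2 × mean visit variance / n).
- True SE at visit t = sqrt(2 × SD_t² / n).
- Ratio = sqrt(mean visit variance) / SD_t. Sample size and the absolute SD cancel, so the ratios hold for both age groups.
- Coverage of a nominal 95% interval = 2 × Φ(1.96 × ratio) − 1.

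| Assumed SDs, weeks 6/12/26/52 (week 52 = 1) | Mean variance | Its root | Ratio week 6 | Ratio week 52 | Coverage week 6 / week 52 |
|---|---|---|---|---|---|
| 1.40/1.27/1.13/1.00 | 1.462 | 1.209 | 0.86 | 1.21 | 91.0% / 98.2% |
| 1.20/1.13/1.07/1.00 | 1.216 | 1.103 | 0.92 | 1.10 | 92.8% / 96.9% |
| 1.00 throughout | 1.000 | 1.000 | 1.00 | 1.00 | 95% / 95% |
| 0.80/0.87/0.93/1.00 | 0.816 | 0.903 | 1.13 | 0.90 | 97.3% / 92.3% |

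A REML simulation (69 per arm, 80 runs per pattern, correlation 0.75 per visit) agrees. With SDs falling from 20.9 to 14.9, the model SE was 3.03 at all four visits, against true SEs of 3.55, 3.22, 2.87 and 2.54. Ratios at weeks 6 and 52 were 0.85 and 1.19 with falling SDs, 0.99 and 0.99 with constant SDs, and 1.13 and 0.91 with rising SDs.

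**Part 2: pre-injury DASH as an outcome visit.** Suppose its SD is half the week-52 SD (assumed).
- Equal later SDs: mean variance = (0.25 + 4 × 1)/5 = 0.85, root 0.92. The ratio is 0.92 at every post-injury visit, with a type I error of about 7%.
- Week-6 SD 1.2 times the week-52 SD: mean variance = (0.25 + 4.862)/5 = 1.022, root 1.011. Ratios are 1.011/1.2 = 0.84 at week 6 and 1.01 at week 52.

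**Part 3: equal SDs, decaying correlation.** Let the correlation be 0.75 per visit step (assumed).
- The six visit pairs have correlations 0.75 (three pairs), 0.5625 (two) and 0.4219 (one), with mean (2.25 + 1.125 + 0.4219)/6 = 0.6328. The random-intercept model uses this mean for every pair.
- For the difference between the week-6 and week-52 treatment effects, the true variance is proportional to 1 − 0.4219 = 0.5781 and the model variance to 1 − 0.6328 = 0.3672.
- SE ratio = sqrt(0.3672/0.5781) = 0.80. Type I error = 2 × Φ(−1.96 × 0.80), about 12%.
- For decay of 0.6 to 0.85 per step, the type I error runs from about 10% to 13%.

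**The case against.** The tempting stronger reading is that the intervals will be too narrow at week 6 and too wide at week 52, so that precision is lost on the main question. The article does not support this.
- That direction needs the spread to fall over time, and no visit-specific SD is given. A rising spread is conceivable: at 6 weeks non-surgical patients are still braced or just being tested for stability, and later they divide into healed, crossed-over and nonunion groups. The week-52 excess also nearly vanishes if a low-variance pre-injury score is modelled as an outcome.
- The primary week-52 comparison is a separate linear regression and does not use this model.
- Earlier DASH scores are not tied to the mixed model. Primary analysis also provides a t-test or non-parametric test for numerical comparisons, and a test at a single visit uses that visit's own variance.
- A random intercept does not exclude heterogeneous residuals or robust standard errors, and the statistical analysis plan, which is not shown, may specify them. The coding of time is open too.

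All of this stands, and it limits the point to a direction-neutral remark on a secondary model. It does not remove the point. The article lists the model's components and gives the random intercept as the only within-patient term. Read with ordinary residuals, that is compound symmetry. Part 3 also shows an error in the interaction that needs no difference in variance.

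**Conclusion.** The point holds as a recommended improvement to a secondary analysis. As written, and with ordinary residuals, the longitudinal model's visit-specific and interaction inference is valid only under equal variance and equal correlation. Under moderate assumed departures, visit-specific SEs are off by roughly 8% to 21% in either direction, and the week-6-versus-week-52 interaction SE is about 20% too small. With equal variances and equal correlations there is no error.

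These sizes rest on assumed SD ratios and correlation decay, categorical time, four outcome visits and complete data. The sign of the visit-specific error cannot be settled from the article, and the primary result is not touched.

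**What to change.** Specify the longitudinal model with visit as a category, a treatment-by-visit interaction and an unstructured within-patient covariance. State which visits enter. Name the fallback in advance for non-convergence: a heterogeneous-variance structure with robust standard errors. Enter pre-injury DASH as a covariate, not as an outcome visit. One caution is that Baseline data has this score collected just after randomisation, so adjusting for it assumes that recall does not depend on the allocation.

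The cost is wording plus a few parameters. Four visits need 4 × 5/2 = 10 covariance parameters instead of 2. After 15% attrition about 139 (163 × 0.85) and 105 (124 × 0.85) patients remain, which is enough to estimate them. The remaining downside is possible non-convergence, which the fallback covers. The remedy works whichever way the spread changes over time.
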